### **Data management**

[name] from Chinese Center for Health Education will work with staff of research team to maintain quality assurance for all data. The process will be checked according to Standard Protocol Items: recommendations for interventional trials. All the data will be stored in Peking University and are password-protected. All patients' information is only accessible for personnel participating in the study. For statistical analysis, all patients' information will be encoded in order to guarantee personal information and unidentifiable during processing or reporting the result. The number of patients who drop out will be reported.

### **Sample size**

The sample size calculation was based on the formula for a two-arm RCT. Based on earlier research, we estimated that biochemically verified continuous smoking abstinence at 6 months would be approximately 4% in the control group and 10% in the intervention groups. To achieve 80% power with a significance level of .05 (two sided), a sample size of 280 individuals was needed in each group. Assuming 20% attrition in the follow-up measurements, the total required sample size was 672.

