### **Randomization**

An independent statistician, [name] [name] from Guanghua School of Management, Peking University, will oversee the randomization but will not be involved in the treatment. After recruitment, participants were required to complete the baseline questionnaire and register through WeChat. With a randomized block design and the score of the Fagerström Test for Nicotine Dependence as a stratified factor, eligible participants were assigned to the intervention group or the control group. The WeChat system was also used to balance demographic characteristics. Randomization was fully computerized and automated with equal allocation. The researchers and participants were all blinded.

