### **Statistical analysis**

Descriptive statistics will be conducted to compare the baseline status between the two groups.

Data will be analyzed on an intention-to-treat (ITT) basis. In accordance with the ITT principle, all patients will be included in the analysis, independently of the groups to which they are randomly assigned and regardless of whether they complete the treatment or not. Participants who breach the protocol (taking cessation medication or received other cessation treatment) will be followed-up in their original group and classified according to their smoking status consistent with other participants.

The Russell Standard (RS) will be used in this study. All randomized subjects will be included in the denominator for calculating abstinence rates with the exception of unavoidable loss to follow-up (died or moved to an untraceable address). Those who decline to be involved in subsequent data collection will be counted as smokers. This type of analysis is considered the most conservative and is the standard for smoking cessation studies.

The primary and secondary abstinence outcomes will be analyzed by logistic regression of smoking status at each timepoint. The dependent variable is smoking

status (still smoking=0, abstinent=1). The independent variable is each intervention versus the control condition. Odds ratios (Or) will be used to measure the outcomes for the intervention groups compared to the control group, and 95% confidence intervals (CI) and P values will be reported to infer efficacy. In sensitivity analyses, each model will be further adjusted for baseline covariates: living area, age, education, smoking frequency and nicotine dependence at baseline.

All data will be analyzed using SPSS version 21.0. The level of bilateral significance for all statistical tests will be established at  $\alpha = 0.05$ .

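### The 20% attrition uplift treats lost participants as leaving the analysis, but the primary analysis keeps most categories of loss as smokers, so the 80% power stated for 672 does not describe that analysis

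*Protocol*

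**What the plan says.** The Sample size section of the protocol sets its target as follows: "To achieve 80% power with a significance level of .05 (two sided"), "a sample size of 280 individuals was needed in each group". The planning rates are introduced with "Based on earlier research, we estimated that", followed by "biochemically verified continuous smoking abstinence at 6 months would be approximately 4% in the control group and 10% in the intervention groups". The attrition step is: "Assuming 20% attrition in the follow-up measurements, the total required sample size was 672". The Randomization section confirms 1:1 allocation ("Randomization was fully computerized and automated with equal allocation"), so 672 means 336 per group.

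The Statistical analysis section adopts intention to treat with the Russell Standard. Its denominator rule is: "All randomized subjects will be included in the denominator for calculating abstinence rates with the exception of unavoidable loss to follow-up", where the exception covers participants who have died or cannot be traced after moving. For refusers it says: "Those who decline to be involved in subsequent data collection will be counted as smokers".

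Two facts are not given. The Sample size section does not say whether 4% and 10% are rates among all randomised or among those followed up. Neither section says how much of the 20% is expected to be refusal and how much unavoidable loss.

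**The concern.** Enlarging a sample for attrition makes sense when lost participants leave the analysis: enough must be randomised for 280 per group to remain. Under the rule in the Statistical analysis section, a participant lost through refusal stays in the denominator and is scored as smoking. That loss does not reduce the number analysed. It pulls down both abstinence rates and the difference between them. Only unavoidable loss reduces the number analysed.

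The size of the trial and its primary analysis therefore rest on different treatments of missing outcomes. At stake is the power claim for the primary outcome: a reader cannot tell whether 672 gives a margin above 80% or falls a little short.

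**Working it through.** **Inputs.** From Sample size: 4% and 10%, two-sided alpha 0.05, power 80%, attrition 20%, total 672. From Randomization: equal allocation. From Statistical analysis: the denominator rule and the scoring of refusers. Assumed here: attrition is equal in the two groups, and everyone not unavoidably lost but missing is counted as a smoker.

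**1. The plan's own figures.** The unpooled two-proportion formula is n = (1.960 + 0.842)² × [p1(1−p1) + p2(1−p2)] / (p2−p1)², with (1.960 + 0.842)² = 7.849.

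n = 7.849 × (0.04×0.96 + 0.10×0.90) / 0.06² = 7.849 × 0.1284 / 0.0036 = 279.9, so 280 per group, as stated. (With pooled variance under the null it is 283.) Then 280 × 1.2 = 336 per group, and 336 × 2 = 672, also as stated.

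**2. If all lost participants did leave the analysis.** Retaining 280 after 20% loss needs 280 / 0.8 = 350 per group, 700 in total. Multiplying by 1.2 instead leaves 336 × 0.8 = 268.8 per group. Power = Φ(difference / SE − 1.960):

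0.06 / √(0.1284/268.8) = 2.745, and Φ(2.745 − 1.960) = 78.4%.

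**3. If 4% and 10% already count refusers as smokers.** Refusal then needs no further allowance. Let u be the proportion of participants unavoidably lost; the number analysed is 336(1−u) per group at 4% v 10%.

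| u | analysed per group | power |
|---|---|---|
| 0% | 336 | 86.6% |
| 5% | 319.2 | 84.9% |
| 10% | 302.4 | 82.9% |
| 16.7% | 280 | 80.0% |
| 20% | 268.8 | 78.4% |

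The 80% point is where 336(1−u) = 280, so u = 1 − 280/336 = 16.7%. With u = 0, 560 in total (2 × 280) would suffice.

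**4. If 4% and 10% are rates among those followed.** The 80% followed supply all the abstainers. With u unavoidably lost, the analysed number is 336(1−u) and each rate is multiplied by 0.8/(1−u).

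- u = 0: rates are 0.8 × 4% = 3.2% and 0.8 × 10% = 8.0%. The variance sum is 0.032×0.968 + 0.08×0.92 = 0.1046. Then 0.048 / √(0.1046/336) = 2.72, and power is Φ(2.72 − 1.96) = 77.7%. The size for 80% is 7.849 × 0.1046 / 0.048² = 356.3, so 357 per group, 714 in total.
- u = 10%: 302.4 per group, 3.56% v 8.89%, power 78.0%.
- u = 20%: 268.8 per group, 4% v 10%, power 78.4%, as in step 2.

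On this basis power stays between 77.7% and 78.4% at every split.

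**5. Sensitivity to formula.** With pooled variance the main figures are 86.3% (step 3, u = 0), 77.3% (step 4, u = 0) and 78.0% (all loss excluded). The pattern does not change.

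**The case against.** The strongest reply has three parts.

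First, the denominator rule does exclude unavoidable loss, so some allowance for attrition is legitimate. This stands. A reader might infer that 672 cannot give 80% on any reading, or that nearly all lost participants will remain as smokers. The protocol supports neither inference. It gives no split of the 20%, and step 3 shows that 672 gives 80% if about 16.7% of participants are unavoidable losses. That is five-sixths of all attrition, which the text permits but does not state or justify.

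Second, the planning rates describe the primary outcome, and the protocol itself calls its treatment of refusers standard in this field, so 4% and 10% may well already be on that basis. Power would then exceed 80% unless unavoidable loss passes 16.7%. This is plausible, but the Sample size section cites only earlier research and does not state the denominator.

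Third, the worst case is a shortfall of about 2 points on rates the protocol calls approximate. That is also fair. At 336 per group, moving the intervention rate from 10% to 9.5% takes power from 86.6% to 81.6% by the same formula, a larger change. It limits the importance of the point, but the attrition step and the denominator rule still disagree.

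**Conclusion.** The point holds in a limited form. The attrition step assumes that all lost participants leave the analysis, whereas the analysis rule removes only unavoidable losses and scores refusers as smokers. The 80% attached to 672 is therefore not derived for the primary analysis. Depending on two unstated facts, the power of 336 per group runs from about 78% to about 87%. Even on the assumption behind the uplift, the arithmetic gives 700 rather than 672.

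These figures rest on the unpooled formula that reproduces 280, on 20% attrition in each group, and on the planning rates being right. They do not show that the trial is materially underpowered: the largest shortfall is 2.3 points, and on one plausible basis there is a surplus.

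**What to change.** In the Sample size section:

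1. Establish from the source of the 4% and 10% whether they are rates among all randomised with missing counted as smoking, or among those followed, and state it.
2. State the assumed share of participants who will be unavoidably lost, within the 20%.
3. Allow for attrition only for that share, dividing by one minus it. Do not remove the allowance altogether, because the analysis rule does exclude these participants.
4. Treat the rest of the 20% as smokers in the planning rates, unless the source rates already do so.
5. Restate the power of 336 per group on that basis. If the basis of the source rates cannot be established, report the range of about 78% to 87%.

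The cost is a rewording of the sample size paragraph, with no extra participants. The one drawback is that the restated power may come out slightly below 80%.

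### The total of 672 covers 16.7% attrition, not the stated 20%; the effect on power is small and depends on how losses enter the abstinence rates

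*Protocol*

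**What the plan says.** The Sample size section assumes biochemically verified continuous abstinence at 6 months of "approximately 4% in the control group and 10% in the intervention groups". With 80% power and a two-sided 0.05 level it concludes that "a sample size of 280 individuals was needed in each group". The next sentence makes the allowance for loss: "Assuming 20% attrition in the follow-up measurements, the total required sample size was 672". No inflation formula is given. The Randomization section fixes 1:1 allocation ("Randomization was fully computerized and automated with equal allocation"), so the total before attrition is 560, and 672 means 336 per group.

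The Statistical analysis section sets out how losses are treated under the Russell Standard: "All randomized subjects will be included in the denominator for calculating abstinence rates with the exception of unavoidable loss to follow-up", where unavoidable means death or a move to an address that cannot be traced. For refusals the rule is: "Those who decline to be involved in subsequent data collection will be counted as smokers".

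**The concern.** An attrition rate is normally a fraction of those enrolled. To have n left after losing a fraction d, one enrols n/(1 - d), not n x (1 + d). The total of 672 matches the second form exactly, so the number left after the assumed loss is smaller than the number that the preceding sentence calls necessary. The two sentences cannot both hold.

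At stake is whether the stated total delivers the stated power at the stated attrition. The same paragraph is also silent on a linked matter: whether the 4% and 10% are rates among everyone randomized, with losses counted as smokers, or rates among people actually followed up. That choice decides what attrition does to power under the protocol's own analysis rule.

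**Working it through.** **Inputs.** Sample size section: p1 = 0.04, p2 = 0.10, 80% power, two-sided alpha 0.05, 20% attrition, 280 per group, total 672. Randomization section: equal allocation. Statistical analysis section: losses stay in the denominator as smokers unless unavoidable.

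**1. Reproduce 280.** Two-proportion normal approximation with unpooled variance:

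n = (1.95996 + 0.84162)^2 x (0.04 x 0.96 + 0.10 x 0.90) / 0.06^2 = 279.94, so 280 per group.

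This matches the protocol. The pooled-variance version gives 283, which is close. The base figure is sound.

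**2. Reproduce 672.** 2 x 280 = 560, and 560 x 1.2 = 672 exactly. The division form gives 560/0.8 = 700, which does not match. That 20% was added to 560 is an inference from this exact agreement, since the protocol shows no formula.

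**3. Test 672 against 20% attrition.**
- Remaining: 672 x 0.8 = 537.6, or 268.8 (about 269) per group, against 280 needed.
- Shortfall in the total: 700 - 672 = 28, which is 28/700 = 4%.
- Largest loss that leaves 560: 1 - 560/672 = 16.7%.

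**4. Power.** Using power = Phi(|p2 - p1| / sqrt[(p1(1 - p1) + p2(1 - p2))/n] - 1.95996), the unpooled form that gives 280:

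| Reading | Rates | n per group in denominator | Power |
|---|---|---|---|
| A. All 20% leave the denominator | 4% vs 10% | 269 | 78.4% |
| B. Losses stay in as smokers; rates already include them | 4% vs 10% | 336 | 86.6% |
| C. Losses stay in as smokers; rates describe only those followed up | 3.2% vs 8% | 336 | 77.7% |

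Reading A with pooled variance gives 78.0%, against 79.6% at 280 by that same formula.

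In reading C, 20% counted as smokers in each group turns the rates into 0.8 x 4% = 3.2% and 0.8 x 10% = 8%. The required number is then (1.95996 + 0.84162)^2 x (0.032 x 0.968 + 0.08 x 0.92) / 0.048^2 = 356.3, so 357 per group. Even 350 per group (700 in total) gives only 79.3%.

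Reading B assumes no unavoidable loss. With 5% unavoidable loss power is 84.9%, with 10% it is 82.9%, and it reaches 80% at a loss of 16.7%.

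**The case against.** The strongest reply is that the analysed sample will not fall to 269 per group. The protocol rejects a completers' denominator: only participants who died or cannot be traced are removed, and those who decline are counted as smokers. The phrase about attrition in the follow-up measurements does not say that all 20% are of the unavoidable kind. If the 4% and 10% already count losses as smokers, 336 per group gives more than 80% power, and the trial is larger than it needs to be.

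This stands as far as consequences go. A reader might infer from step 3 that the trial will analyse 269 per group with 78% power and is therefore underpowered. The documents do not support that as a general statement; it holds only if every loss is unavoidable.

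The reply does not rescue the stated total. The Sample size section itself treats attrition as the reason to enlarge the sample, and on that premise the enlargement does not leave 280. In reading C, 672 also falls short of 80% power. In reading B, losses that stay in the denominator call for no allowance at all, so the reason given for 672 would be wrong in another way.

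It is also fair to say that the inputs are approximate and that a difference of 28 participants is small beside their uncertainty. That bears on severity, not on whether the sentence is correct.

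**Conclusion.** The attrition step is wrong as written; the base figure of 280 is correct. A total of 672 matches 16.7% loss from the denominator, and the stated 20% would correspond to 700, so the total is 28 participants (4%) short of its own premise.

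If all 20% left the denominator, the cost would be about 1.6 points of power (80% to 78.4%). Under the protocol's Russell Standard rule the power of 672 lies elsewhere: about 86.6% or about 77.7%, depending on an assumption about the 4% and 10% that is not stated. Both of those figures take all losses as kept in the denominator, and the second also takes the 20% loss as equal in the two groups. The documents therefore do not establish that the trial is underpowered, only that its sample size statement does not follow from its own figures.

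The slip does not touch the type I error or the validity of the primary comparison. Severity: minor.

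**What to change.** Correct the Sample size section without enrolling more participants:

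1. Replace the attrition sentence with one saying that 672 (336 per group) allows for a 16.7% loss from the denominator at 80% power, where 4% and 10% are the rates in that denominator. Note that a 20% loss would correspond to 700.
2. State whether the 4% and 10% already count losses as smokers, as the Statistical analysis section requires, or apply only to people followed up.
3. Restate the power of 672 on that basis: about 86.6% in the first case if no loss is unavoidable (lower as unavoidable losses rise, reaching 80% at 16.7%), or about 77.7% in the second with 20% counted as smokers in each group.

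The figure of 269 per group with 78.4% power should appear only with the condition that all 20% are unavoidable losses. Nor should 700 be presented as a sure remedy, because in the second case about 357 per group would be needed.

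The cost is two or three sentences of protocol text. The stated attrition tolerance becomes slightly less favourable; the stated power may go up or down according to item 2.
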